#### Statistical Analyses

Statistical methods used in the analysis of this study will include descriptive statistics with the descriptive presentation of the total sample value, mean, SD, median, minimum, maximum, and 95% CIs for (pseudo) continuous data and categorical data. Further evaluations will be summarized in tables by counts and percentage of scores.

Statistical methods for primary study end points will include the following: the Shapiro-Wilk test of normality on calculated values (in case of normal distribution, a 2-sided independent *t* test and in case of nonnormal distribution: a 2-sided Mann-Whitney *U* test) and a linear mixed model with the random factors “center” and “study arms by center.”

Designated as study arm C, the never-smoker group will establish a baseline reference for the oral health parameters. This group is anticipated to provide insights into the underlying changes in the primary study end point (MGI) that may emerge over time in individuals who have never smoked.

Statistical methods for secondary study end points will include the following: for comparisons of each study arm for parameters such as MGI assessment, plaque imaging, dental shade quantitation, tooth stains scores, and oral health–related quality of life questionnaires, the Shapiro-Wilk test of normality on calculated values (in case of normal distribution, a 2-sided independent *t* test and in case of nonnormal distribution: a 2-sided Mann-Whitney *U* test); for comparisons of each assessment time for parameters such as MGI assessment, plaque imaging, dental shade quantitation, tooth stains scores, and oral health–related quality of life questionnaires, the Shapiro-Wilk test of normality on calculated values (in case of normal distribution, a 2-sided independent *t* test and in case of nonnormal distribution: a 2-sided Mann-Whitney *U* test); accounting for missing, unused, and spurious data.

If only one value of the parameter MGI is missing after day 1, the last available observation will be carried forward. The analysis will be performed on the substituted data. For secondary parameters, no replacement of missing values will be applied.

A generalized linear regression model will be used to adjust for all identified confounders. To identify possible predictors of primary and secondary study end points, a regression model will be estimated in which each study end point will be entered as the dependent variable. Possible predictors will be entered into the model as independent variables (including study group; age; gender; cigarette consumption; combustion-free nicotine delivery systems use; and frequency of personal oral hygiene, eg, tooth brushing, mouth washing, and dental flossing frequency) to assess the interactions. Following the results obtained from each regression model, comparisons between and within study groups will be performed using analysis of covariance adjusted for age, gender, and frequency of personal oral hygiene followed by the Tukey post hoc comparison test.

The goal of our study is to help smokers abstain from cigarette smoking to assess changes in oral health regardless of the product used. This study is not designed to compare the efficacy between HTPs and ECs in terms of smoking cessation. Nonetheless, we will consider a secondary analysis that takes into account the potential different impact of HTPs versus ECs in terms of oral health outcomes.

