**Methods:**

Regular smokers not intending to quit and without clinical signs of periodontitis will be randomly assigned (1:4 ratio) to either standard of care with brief cessation advice (control group; arm A) or C-F NA use (intervention group; arm B). The study will also include a reference group of never smokers (reference group; arm C). The primary end point is the change in the Modified Gingival Index (MGI) score from baseline between the control arm (arm A) and the intervention arm (arm B) at the 18-month follow-up. In addition, the study will analyze the within- and between-group (arms A, B, and C) changes in MGI assessment, plaque imaging, dental shade quantitation, tooth stain scores, and oral health–related quality of life questionnaires measured at each study time point. All participants will attend a total of 7 clinic visits: screening, enrollment, and randomization (visit 0); baseline visit—day 14 (visit 1); day 90 (visit 2); day 180 (visit 3); day 360 (visit 4); and day 540 (visit 5). This multicenter study will be conducted in 4 dental clinics in 4 countries. The statistical analysis will involve descriptive statistics for continuous and categorical data. Primary end points will undergo tests for normality and, based on distribution, either a 2-sided *t* test or Mann-Whitney *U* test. Linear mixed model with random factors center and study arms by center will also be applied. Secondary end points, including MGI assessment and quality of life, will be subjected to similar tests and comparisons. Only if one value of the parameter MGI is missing after day 1, the last available observation will be carried forward. The analysis will be performed on the substituted data. Secondary parameters will not have missing value replacement.

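### The primary analysis is chosen by a normality pre-test, sits beside an unranked random-centre mixed model, and no described analysis names baseline MGI as a covariate

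*Protocol article*

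**What the plan says.** The Abstract (Methods) defines the outcome: "The primary end point is the change in the Modified Gingival Index (MGI) score from baseline between the control arm (arm A") and arm B at 18 months. On the analysis it says "Primary end points will undergo tests for normality and, based on distribution, either a 2-sided" t test or a Mann-Whitney U test is used, and then: "Linear mixed model with random factors center and study arms by center will also be applied".

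The Statistical Analyses section repeats this for the primary end point: "the Shapiro-Wilk test of normality on calculated values (in case of normal distribution, a 2-sided independent" t test, and in the non-normal case a 2-sided Mann-Whitney U test, "and a linear mixed model with the random factors" centre and arm-by-centre. Only the random factors of that model are given.

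Later in the same section, each study end point is regressed on possible predictors, "including study group; age; gender; cigarette consumption; combustion-free nicotine delivery systems use; and frequency of personal oral hygiene". Group comparisons then follow by "analysis of covariance adjusted for age, gender, and frequency of personal oral hygiene followed by the Tukey post hoc comparison test". Baseline MGI is in neither list.

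The Sample Size Calculation section states the hypothesis in terms of mean changes (µA and µB) and sizes the trial with a t test. The trial runs in four clinics in four countries.

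**The concern.** Three features of the primary analysis work together.

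- **The outcome data choose the test.** The t test compares mean changes, which matches the stated hypothesis and the sample size. The Mann-Whitney test asks whether values in one arm tend to exceed those in the other. If the Shapiro-Wilk test rejects, the reported P value no longer answers the question the trial was sized for.
- **Two analyses of the same contrast are unranked.** A random arm-by-centre term estimated from four centres can give a much weaker test than the two-sample t test. The document does not say which result decides if they differ.
- **Baseline MGI enters only by subtraction.** It is measured in everyone and is likely to predict month-18 MGI, but no described analysis names it as a covariate.

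At stake are an unambiguous primary result and some precision that could be had from data already collected.

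**Working it through.** **Inputs from the document.** Difference 0.10; SD of change 0.21; 77 per group before dropout; 92 per group after dropout; dropout 20%; 25% of arm B expected to switch; 368 in arm B; four centres; 1-sided 5% and 90% power for the sample size; 2-sided tests in the analysis.

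**Assumed, because the document gives no figure.** Correlation r between baseline and month-18 MGI; ratio k of baseline SD to month-18 SD; SD τ of the arm effect across centres; the df method of the mixed model; the shape of the outcome distribution.

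**Step 1. The plan's own figure.** The exact noncentral-t calculation for 0.10, SD 0.21, 1-sided 5% gives power 0.899 at 76 per group and 0.903 at 77. The stated 77 is reproduced, as are all 15 cells of Table 5.

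**Step 2. Reference power.** If arm B is analysed as switchers only, it has 0.25 × 368 = 92, and after 20% dropout 0.8 × 92 = 73.6, taken as 74; arm A likewise. SE = 0.21 × √(2/74) = 0.0345. The 2-sided t test then has 82% power.

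**Step 3. The pre-test.** Simulation used 4,000 trials per setting, with normal, gamma(4), exponential and t(5) data, at 77/77 and 74/294, and Shapiro-Wilk applied in each arm.

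| Quantity | Range over settings |
|---|---|
| Type I error of the two-stage procedure | 0.050 to 0.054 (0.048 in one setting) |
| Type I error if either test could be reported | 0.056 to 0.072 |
| t and Mann-Whitney disagree on significance, true difference 0.10 | 2% to 15% |

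**Step 4. The mixed model.** With roughly equal centres, SE² = 0.21² × 2/74 + τ²/4. The t reference has 3 df if two arms enter (1 × 3) and 6 df if all three arms enter (2 × 3).

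| τ | SE | Power, 3 df (critical t 3.18) | Power, 6 df (critical t 2.45) |
|---|---|---|---|
| 0 | 0.0345 | 51% | 68% |
| 0.05 | 0.0426 | 37% | 50% |

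With a normal reference the corresponding figures are 83% and 65%, so the df method drives much of the gap.

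**Step 5. Baseline adjustment.** With month-18 variance s², Var(change) = s²(1 + k² − 2rk), and the ANCOVA residual variance is s²(1 − r²). The variance ratio is (1 − r²)/(1 + k² − 2rk), which is (1 + r)/2 when k = 1. It cannot exceed 1, because (1 + k² − 2rk) − (1 − r²) = (k − r)² ≥ 0. Power at 74 per group, with the SD of change held at 0.21:

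| k | r = 0.3 | r = 0.5 | r = 0.7 |
|---|---|---|---|
| 1.0 | 0.65 → 95% | 0.75 → 91% | 0.85 → 88% |
| 0.7 | 0.85 → 88% | 0.95 → 84% | 1.00 → 82% |
| 0.5 | 0.96 → 84% | 1.00 → 82% | 0.93 → 85% |

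Each cell shows the variance ratio and the resulting power, against 82% unadjusted.

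**The case against.** The strongest reply is that little harm is shown and much is left open for a fuller document.

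- **Type I error.** A reader might infer that the pre-test inflates it. Step 3 does not support that: the two-stage procedure stayed near 5%. The rule is also mechanical and prespecified, so whether analysts could recognise the arms from their sizes has no bearing on it. This part of the reply stands.
- **How often the switch fires.** A reader might call the choice of test a coin toss. The rate depends wholly on the assumed shape: about 10% for normal data, and from 22% to 99% over a range of gamma skewness. The document gives nothing on the distribution of MGI change, so no single rate can be claimed.
- **Baseline.** A reader might infer that no analysis adjusts for baseline MGI. The mixed model's fixed effects are not stated, the predictor list is open, and adjustment for identified confounders is promised. Only the ANCOVA list ("adjusted for age, gender, and frequency of personal oral hygiene") is closed and omits it. The Discussion also says that scaling and polishing reduced baseline variability, so k below 1 is plausible and the gain may be nil.
- **Mixed model.** The 3 df are not stated in the plan. The Abstract's wording hints that this model is supplementary, but a hint is not a ranking.
- **Group size.** If all arm B completers are analysed (74 against 294), the 2-sided t test has 95% power for a difference of 0.10, so the shortfall from 82% is specific to the switcher-only reading. The gap to the mixed model remains there (69% with 3 df).

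What the reply does not remove is that the document affirmatively prescribes a data-driven switch and a parallel model. That is a stated choice, not an omitted detail.

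**Conclusion.** The point holds in a limited form. The plan lets the data choose between tests of two different hypotheses, only one of which matches the sample-size hypothesis. It adds a second model for the same contrast without ranking the two, and names baseline MGI as a covariate nowhere.

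The harm is ambiguity about what is tested and which result counts, not a demonstrated excess of false positives. Its size is:

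- disagreement between the t and rank tests in about 2% to 15% of simulated trials;
- mixed-model power of about 51% to 68% with no heterogeneity, against 82%, if a small-df reference is used;
- a gain from baseline adjustment of between nothing and 13 percentage points (82% to 95%) over r from 0.3 to 0.7 and k from 0.5 to 1. Asymptotically it is never a loss.

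All of these rest on assumed distributions, correlation, SD ratio, heterogeneity and df method.

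**What to change.** Delete the Shapiro-Wilk switch. Before unblinding, name one primary analysis: month-18 MGI (or its change) by ANCOVA or a repeated-measures mixed model, with arm, baseline MGI and centre as a fixed four-level factor, 2-sided at 5%. Use robust or bootstrap intervals if residuals are skewed. Label the Mann-Whitney test and the random arm-by-centre model as sensitivity analyses, and state the df method for the latter.

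No new data are needed, since baseline MGI and centre are already recorded. The cost is a dated and justified amendment, because enrolment closed in June 2023 and the change must be seen to precede access to outcomes by arm.

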### Statistical Considerations

#### Sample Size Calculation

For a valid sample size calculation, literature research was performed for the primary end point of the study (ie, MGI). Unfortunately, no data were available for such a study. However, data from studies with mouth rinse were available, and based on these studies [30,31], a mean MGI change of 0.08 with an SD of 0.18 of the MGI seemed relevant.

However, in these studies, higher mean MGI changes were observed because active treatment was administered, which was not the case in this study. Thus, several scenarios with different mean MGI changes and SDs will be applied.

The following hypotheses will be tested with a 1-sided independent *t* test:

H0: µA≤µB versus H1: µA>µB

where µA denotes the mean change MGI from baseline to after 18 months of regular smoking and µB denotes the mean MGI from baseline to after 18 months of C-F NA use.

For sample size calculation, SAS software (version 9.4; SAS Institute) was used and several scenarios were applied, assuming that the data are normally distributed. The results are summarized in Table 5, which presents the calculated sample sizes for the comparison of µA versus µB by a 1-sided independent *t* test, a significance level of 5%, and a power of 90%, depending on the expected MGI change and SD.

As no active treatment is given in this study, a lower effect than the observed values needs to be assumed. Therefore, a mean MGI change of 0.1 with an SD of 0.21 was chosen. Hence, a sample size of 77 patients per treatment group is required. Considering a dropout rate of 20% over 2 years’ observation phase [32,33], a sample size of at least 92 per treatment group is required. In addition, it is estimated that approximately 25% of those switching to C-F NA use will abstain or substantially (≥90%) reduce smoking [34], and only these participants deliver valid results. Therefore, 4 times more participants should be recruited in the C-F NA group (4 × 92 = 368). This results in a total sample size of 460 (92 in arm A+368 in arm B).

In arm C, we have determined a sample size of 40, empirically with no formal statistical analysis, as this cohort’s primary study end point (ie, MGI) is expected to be stable throughout the study.

**Table 5 table5:** Summary table including the sample size for each arm of the study depending on the mean Modified Gingival Index (MGI) change and SD.

Nominal power	Mean MGI change	SD^a^				
		0.20	0.21	0.22	0.23	0.24

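### A Shapiro-Wilk pre-test on the trial's own data chooses the primary test, so a hypothesis stated and sized in mean MGI change may be tested on ranks instead

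*Protocol article*

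**What the plan says.** Under Statistical Analyses, the primary end point first undergoes "the Shapiro-Wilk test of normality on calculated values"; the result then selects the test: "in case of normal distribution, a 2-sided independent *t* test and in case of nonnormal distribution: a 2-sided Mann-Whitney *U* test". The abstract's Methods paragraph gives the same rule: "Primary end points will undergo tests for normality and, based on distribution, either a 2-sided *t* test or Mann-Whitney *U* test".

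Both places also list a linear mixed model. The abstract says: "Linear mixed model with random factors center and study arms by center will also be applied". Neither place says whether the model or the pre-tested pair gives the primary result.

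The Sample Size Calculation section is written in means throughout. µA "denotes the mean change MGI from baseline to after 18 months of regular smoking", the hypotheses compare µA with µB, the chosen effect is a mean difference of 0.1 with SD 0.21, and the size is computed for a t test "assuming that the data are normally distributed".

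Statistical Analyses repeats the Shapiro-Wilk rule for the secondary end points, both between arms and between assessment times.

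**The concern.** The t test compares mean changes and gives a difference in MGI units. Mann-Whitney asks whether a value from one arm tends to exceed a value from the other. The two coincide when the arms differ only by a shift, but not when their shapes differ. Different shapes are plausible here, because the plan itself expects only about 25% of arm B to abstain or cut smoking by at least 90%.

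Shapiro-Wilk becomes more sensitive as the sample grows, which is when the t test needs normality least. In a large arm B, mild skew can move the analysis from means to ranks without any benefit to validity. The stated hypothesis may then be left without its planned test. The mixed model may give a different answer, with no rule for which one counts. For secondary end points, one parameter could be tested on means at one visit and on ranks at the next.

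**Working it through.** **Inputs from the Sample Size Calculation section.** Effect 0.10, SD 0.21, 1-sided 5%, power 90%, 77 per group, dropout 20%, arms of 92 and 368, and about 25% of arm B switching.

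**Assumptions.** The document gives no distribution for MGI change and no level or unit for the Shapiro-Wilk test. I used shifted gamma changes of known skewness and Shapiro-Wilk at 5% in each arm, switching to Mann-Whitney if either arm rejects. Tests are 2-sided at 5%.

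**Step 1: reproduce the plan's figure.** The noncentrality is δ/(σ√(2/n)) = 0.10/(0.21 × √(2/77)) = 2.95 on 152 degrees of freedom. The 1-sided t test then has 90.3% power, so 77 per group is right for a t test on means. The same method matches all 15 cells of Table 5.

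**Step 2: analysed sizes.**
- Arm A: 92 × 0.8 ≈ 74.
- Arm B: 368 × 0.8 ≈ 294.
- Arm B, switchers only: 294 × 0.25 ≈ 74.

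**Step 3: does the t test need protecting?** With the same skewness in both arms:

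| Skewness | Shapiro-Wilk rejects in either arm, 74 vs 294 | Same, 74 vs 74 | t-test type I error |
|---|---|---|---|
| 0.3 | about 52% | about 26% | about 5% |
| 0.5 | about 92% | about 53% | about 5% |

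Over skewness 0.25 to 1.0 at 74 vs 294, the t test's error was 4.7% to 5.2% (20,000 runs per value). The sensitivity lies mainly in arm B: at skewness 0.5, Shapiro-Wilk rejects in 87% of samples of 294 but in 31% of samples of 74. Rounding can also trigger it. Exactly normal changes recorded in steps of 0.1 (assumed) are rejected in every sample of 294; in steps of 1/48, in about 7%.

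**Step 4: does the two-stage rule inflate error?** With identical distributions in the two arms it rejects in 4.8% to 5.6% of trials (4,000 runs), so there is no general inflation.

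**Step 5: does the hypothesis change?** Means and SDs equal, arm A normal, arm B skewed, 74 vs 294 (4,000 runs):

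| Skewness in arm B | t test rejects | Mann-Whitney rejects |
|---|---|---|
| 0.5 | 5.2% | 5.9% |
| 1.0 | 5.3% | 10.1% |
| 1.5 | 5.2% | 14.2% |

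The means do not differ here. Mann-Whitney is responding to shape.

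**Step 6: cost if a minority benefits.** Suppose 25% of arm B benefit by 0.3 or 0.4 (skewness 0.5, 74 vs 294). The mean difference is 0.25 × 0.3 = 0.075 or 0.25 × 0.4 = 0.10.

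| Benefit | Mann-Whitney | Student's t | Unequal-variance mean test |
|---|---|---|---|
| 0.3 | 65.5% | 69.5% | 76.3% |
| 0.4 | 80.8% | 87.4% | 93.1% |

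Shapiro-Wilk rejects in fewer than half of these trials (about 43% to 48%), so the t test is often kept. The two-stage rule therefore loses about 3 to 4 points against always using t. One set of runs gave 65% vs 68% and 82% vs 87%, so single estimates reach 5 points. The t-test verdict changes in about 5% of trials.

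The further gain from Student's t to the unequal-variance test is 76.3 − 69.5 = 6.8 and 93.1 − 87.4 = 5.7 points. It arises because a partial response widens arm B: √(0.21² + 0.25 × 0.75 × 0.4²) = 0.27 against 0.21 in arm A. The pre-test plays no part in that gain.

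**The case against.** The strongest reply is that the rule is prespecified, holds its type I error when the arms share a distribution, and costs nothing under the effect the trial was sized for. With a uniform shift of 0.10 and skewness 0.5, the two-stage rule and the t test have nearly the same power: 82.8% vs 82.1% at 74 vs 74, and 95.8% vs 95.4% at 74 vs 294. All of this stands.

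A reader might infer four stronger things that the document does not support.

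- *The normality test decides whether means are analysed at all.* It does not. The mixed model is listed for the same end point without a pre-test. What is missing is a ranking between it and the pre-tested pair.
- *The pre-test costs 10 to 12 power points.* That is the gap between Mann-Whitney and an unequal-variance test. The plan names an independent t test, and its 77 per group reproduces with the ordinary one.
- *Using ranks inflates type I error when the SDs differ.* With SD 0.26 in arm A, 0.21 in arm B and skewness 1, Mann-Whitney rejected in 9.7% of trials and Student's t in 8.9%. Unequal variances with unequal arms cause this, and removing the pre-test alone would not cure it.
- *The switch is nearly certain.* That depends on who is analysed. The Sample Size Calculation section counts only switchers as giving valid results. At 74 vs 74 the rejection rates fall to 26% and 53%, and the argument about a benefiting minority falls away.

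**Conclusion.** The point holds as a fault in how the primary analysis is fixed. It does not show an invalid test. The pre-test guards against a problem the t test does not have at these sizes, and its outcome decides whether the result concerns the mean difference the trial was sized for. Where the arms differ in shape, this matters: about 10% rejection against 5% with equal means at skewness 1 in arm B only. With a 25% responding minority it costs about 3 to 4 power points and changes about 5% of t-test verdicts. The listed mixed model reduces the harm but does not remove it, because no analysis is named as primary.

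These sizes rest on assumed gamma skewness, a 5% Shapiro-Wilk test in each arm, and 74 analysed in arm A with 74 to 294 in arm B. The step 6 figures also assume positive skew, opposite in direction to the benefit; negative skew would make the pre-test reject more often.

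**What to change.** In Statistical Analyses and in the abstract, delete the Shapiro-Wilk rule. Name in advance one mean-based analysis of the arm A versus arm B difference in MGI change at 18 months as primary, reported with a 95% CI. This can be the linear mixed model already listed, or a linear model accounting for center with standard errors that allow unequal variances. The second choice, or a mixed model whose residual variance may differ by arm, also addresses the unequal-variance problem, which is a separate reason to prefer it. Keep Mann-Whitney as a sensitivity analysis that cannot replace the primary result. Use the same fixed approach for the continuous secondary end points at every visit.

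The cost is wording only, provided the change is made before unblinded analysis. The downside is slightly lower power if the data are strongly skewed and the effect is a uniform shift: about 83% for the t test against 88% for Mann-Whitney at skewness 1 with 77 per group.

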#### Secondary End Points

In addition, the study will analyze the number of secondary objectives, including within- and between-group variations at each study time point from baseline for MGI assessment, plaque imaging, dental shade quantitation, tooth stain scores, and oral health–related quality of life questionnaires.

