### Study Measurements and Calibration

A detailed description of the study measurements that will be specifically carried out at the dental clinic is provided in Multimedia Appendix 2.

All assessors will be trained on MGI scoring, tooth stain assessment, and the correct use of technologies and software used to quantify dental plaque, tooth discoloration, exhaled carbon monoxide monitoring, and electronic case report form (eCRF) use. Assessors will be periodically calibrated on MGI scoring and tooth stain assessment. To ensure consistency in the measurements, the same assessor will collect all study end points in the same participant over the entire study period.

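### Within-arm comparisons between visits are assigned independent-sample tests, which ignore pairing and are conservative; power is lost mainly in the small never-smoker arm

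*Protocol article*

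**What the plan says.** The Secondary End Points section sets objectives "including within- and between-group variations at each study time point from baseline" for MGI, plaque, shade, stain and quality of life. Change over time within an arm is therefore an objective in its own right.

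The Statistical Analyses section gives two separate items for secondary end points. The first is "for comparisons of each study arm for parameters such as MGI assessment, plaque imaging, dental shade quantitation, tooth stains scores" and quality of life. The second is "for comparisons of each assessment time for parameters such as MGI assessment, plaque imaging, dental shade quantitation, tooth stains scores" and quality of life. After a Shapiro-Wilk check, both items get the same tests: "in case of normal distribution, a 2-sided independent *t* test and in case of nonnormal distribution: a 2-sided Mann-Whitney *U* test".

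The visits are repeated measurements. Tables 1 to 3 schedule the same assessments at every visit from enrollment to week 76, and Study Measurements and Calibration states that "the same assessor will collect all study end points in the same participant over the entire study period".

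Two other analyses come near the point. The mixed model is listed for the primary end point, and its only random terms are center and arm by center. Later in the same section, "comparisons between and within study groups will be performed using analysis of covariance adjusted for age, gender, and frequency of personal oral hygiene", followed by Tukey comparisons. Neither states a participant term. The article names no paired t test, signed-rank test or participant-level repeated-measures model.

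**The concern.** Two visits of one arm are two measurements of the same mouths by the same examiner. Their difference has variance 2σ²(1 − ρ), where σ is the SD at a visit and ρ the within-participant correlation. An independent-sample test uses 2σ² instead. If ρ is positive, as is to be expected here, the standard error is too large, P values are too large and real change over time is harder to detect.

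At stake are the secondary within-arm results on MGI, plaque, shade, stain and quality of life. The issue matters most in arm C. It has only 40 participants, and the plan relies on it to show background change in MGI over time. A test that seldom rejects makes an absence of detected change uninformative there.

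**Working it through.** **Inputs from the protocol article.**
- Sample Size Calculation: MGI change 0.10, SD 0.21, 20% dropout; 92 in arm A, 368 in arm B, 40 in arm C.
- Completers, applying the 20% to each arm: A 92 × 0.8 ≈ 74; B 368 × 0.8 ≈ 294; C 40 × 0.8 = 32.

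**Assumptions not in the article.**
- ρ between visits: 0.3, 0.5 and 0.7.
- 0.21 is the SD of the change from baseline, which fits the hypotheses in the Sample Size Calculation because they concern mean changes.
- The 0.10 is the planned difference between arms. It serves here only as a yardstick for a within-arm change.

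**Reproducing the plan's own figure.** A 1-sided independent t test with difference 0.10, SD 0.21, alpha 5% and power 90% gives 77 per group, as stated, and all 15 cells of Table 5 are reproduced. That calculation is for the between-arm comparison. The article gives no figure for the within-arm tests.

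**Standard errors.**
- Paired: 0.21/√n.
- Independent test on the same data: the SD at a visit is 0.21/√(2(1 − ρ)), so SE = 0.21/√(n(1 − ρ)).
- Ratio 1/√(1 − ρ): 1.20, 1.41 and 1.83 at ρ = 0.3, 0.5 and 0.7.

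**True size of the nominal 5% test.** Size = 2[1 − Φ(t_crit/√(1 − ρ))]. With 74 completers t_crit = 1.976:
- ρ = 0.3: 1.976/0.837 = 2.36, size about 1.8%.
- ρ = 0.5: 1.976/0.707 = 2.79, size about 0.5%.
- ρ = 0.7: 1.976/0.548 = 3.61, size about 0.03%.

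A simulation with 77 participants and 4,000 runs gave 1.8%, 0.55% and 0.03% for the t test and 2.0%, 0.6% and 0.03% for Mann-Whitney. The paired t test stayed at 4.5% to 4.9%.

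**Power for a within-arm change of 0.10, 2-sided 5%.** The paired test uses the noncentral t. The independent test uses Φ(0.10/SE_paired − t_crit/√(1 − ρ)), a normal approximation. For arm C, SE_paired = 0.21/√32 = 0.0371, so 0.10/SE_paired = 2.69, and t_crit = 2.00. At ρ = 0.5 this gives Φ(2.69 − 2.83) ≈ 45%.

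| Arm (completers) | Paired | Independent, ρ = 0.3 | ρ = 0.5 | ρ = 0.7 |
|---|---|---|---|---|
| C (32) | 74% | 62% | 45% | 17% |
| A (74) | 98% | 96% | 90% | 69% |
| B (294) | about 100% | about 100% | about 100% | about 100% |

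For a smaller change of 0.05, arm B also loses power at high correlation: 98% paired against 69% at ρ = 0.7.

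**Sensitivity to the SD reading.** If 0.21 is instead the SD of the MGI at a visit, the SD of change at ρ = 0.7 is 0.21 × √0.6 = 0.163. The independent test then has 43% power in arm C, against 92% paired, and 95% in arm A. The loss in arm C remains, but the lowest figures in the table depend on which SD is meant.

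**The case against.** **The wording may mean something else.** The time item could be read as arm comparisons at each visit, for which independent tests are right. The Methods introduction does speak of differences between switchers and continuing smokers at several time points. This reading is possible but weaker: arm comparisons are already the preceding item, and the within-group objective would then have no simple test. The wording would need correcting on either reading.

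**Another within-group analysis is planned.** A reader might infer that every within-group P value in the trial will be wrong. The article does not support that, because the ANCOVA with Tukey comparisons also covers within-group comparisons. As described it adjusts for age, gender and oral hygiene only, so it does not clearly restore the pairing, but the named tests are not the only route to a within-group result.

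**The error is conservative and secondary.** A reader might also infer a risk of false claims of benefit, or damage to the main result. Neither follows. With positive correlation the test rejects too rarely, and the primary contrast compares change between two independent randomized groups.

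**The arm C yardstick is not the plan's scenario.** Stability of MGI in never smokers is an expectation given to justify the choice of 40. It is not a planned test conclusion, so the plan cannot be said to rest a formal claim of stability on this test. The arm C power figures are illustrative.

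These points limit the scope and weight of the finding. None of them makes an independent-sample test appropriate for paired visits.

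**Conclusion.** The point holds as a should-fix. On the natural reading, the plan names a method whose independence assumption the design breaks. This is a stated choice, so it is not a detail left for the statistical analysis plan to fill in.

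The effect is loss of power in secondary within-arm time comparisons. It is substantial in arm C across the assumed correlations, material in arm A only towards ρ = 0.7, and negligible in arm B for a 0.10 change. The size rests on the assumed ρ, on reading 0.21 as the SD of change, and on 20% dropout in every arm. The direction rests only on ρ being positive, which is very likely with the same participant and the same assessor at every visit.

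**What to change.** In the secondary end point paragraph of Statistical Analyses, for comparisons between assessment times within an arm, replace the independent t and Mann-Whitney tests with a paired t test or a Wilcoxon signed-rank test on each participant's change. Visit contrasts from a mixed model with a participant effect are an acceptable alternative, but a paired test is enough. State that independent-sample tests apply to between-arm comparisons only. If the within-group ANCOVA is kept, say how it handles repeated measurements on the same participant.

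The cost is a change of wording and analysis code. No new data are needed, and the primary analysis and sample size are untouched.
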